##### Employment

To cover participation in working life the employment status (employed vs. unemployed) is asked for. Moreover, we will assess if the patients are on sick leave.

##### Subjective prognosis of employment status

Three items assess if patients believe they will remain at work until retirement, if patients assume that their health will be permanently jeopardized, and if patients intend to submit a request for a disability pension [41]. Items are summarized to reflect a total score ranging from zero to three points. Higher values indicate a more unfavorable outcome. A score of at least two points reflects that permanent work participation is deemed to be unlikely.

##### Perceived vocational orientation of the rehabilitation program

The realization of work-related goals and therapies during rehabilitation will be assessed with a slightly modified version of a previously used set of items from a study that investigated the implementation of the WMR guideline [19]. Participants report on 12 dichotomized items as to whether they received WMR contents throughout their rehabilitation program. Scores are aggregated to a total score ranging from zero to 12 points. This score reflects the implementation of the work-related therapies. Additionally, six items assess the perceived diagnostic and therapeutic focus on issues of return to work and work ability, e.g. the experience of a consistent return to work strategy. These items are measured on a five-point scale. Scores will be summed to a total score ranging from zero to 24 points. Finally, the subjective work-related benefit from participating in the rehabilitation program will be assessed by eight items measured on a five-point scale. Scores will be aggregated to a total score ranging from zero to 32 points.

##### Treatment satisfaction

Treatment satisfaction will be assessed using the German version of the Client Satisfaction Questionnaire [42]. This questionnaire includes eight items designed to assess various aspects of the patient’s satisfaction with the treatment. Items are measured on a four-point scale. The sum score ranges from eight to 32 points.

##### Income and welfare benefits

Income from regular employment and the duration of welfare benefits (for example, unemployment and sickness benefit) will be extracted from the GPI accounts.

#### Therapeutic interventions

Therapeutic interventions will be extracted from the standardized rehabilitation discharge letters [19]. These letters are stored in the individual GPI accounts. The documentation of the therapeutic interventions will indicate adherence to the WMR guideline.

#### Department characteristics

Measurement of department characteristics covers amongst others data on average guideline adherence and the number of treated patients. A survey of the departments will assess additional data on the department level (e.g. staff, team cooperation, and infrastructure).

#### Other measures

Additional measures will be assessed as potential effect modifiers and as variables for calculating the propensity score.

##### Risk of not returning to work

Two risk scores are frequently used to assess the need for WMR in Germany. The score of the SIMBO (German: Screening-Instrument zur Feststellung des Bedarfs an medizinisch-beruflich orientierten Maßnahmen in der medizinischen Rehabilitation) [11] ranges from zero to 100 points. Higher scores indicate a higher risk of not returning to work and a stronger need for WMR. A SIMBO score of ≥23 points was shown to be an optimal threshold to identify patients in need for WMR. The Würzburger Screening [12] states a risk of not returning to work and a need for WMR if a person is unemployed at the beginning of the rehabilitation program or scored one out of three points on a three-item scale that assesses negative return-to-work expectations.

##### Somatization

Somatization will be assessed by using seven items from the Symptom Check-List-90-R [43]. All items are measured on a five-point scale (0 = not at all, 1 = a little bit, 2 = moderately, 3 = quite a bit, 4 = extremely). Items are averaged to calculate a total score.

##### Pain generalization

Three newly developed items will assess the experience of widespread pain and pain amplification. These items are measured on a four-point scale (0 = totally disagree, 1 = disagree, 2 = agree, 3 = totally agree). Items are averaged to calculate a total score.

##### Psychosocial stress

Two items will assess family- and job-related stress in the last two weeks [44]. Both items are measured on a four-point scale (0 = not at all, 1 = several days, 2 = more than half of the days, 3 = nearly all days). Items are added to a sum score ranging from zero to six points.

##### Work environment

Several aspects of the work environment will be assessed as they might moderate the treatment effect: amongst others, size of company [45], physical job demands [46], effort-reward imbalance [47], overcommitment [47] and support by co-workers and supervisors.

##### Socio-demographic data

We will ask participants for socio-demographic data (age, sex, native language, educational level, partnership, children, and family life).

### Statistical analysis

#### Propensity score matching

Patients of WMR and CMR will be matched by propensity scores to achieve balanced sample characteristics and to calculate unbiased estimates of relative effectiveness [22, 48–54]. The propensity score is the conditional probability of receiving the treatment under evaluation (i.e. WMR) given the vector of observed background variables. Matching by propensity scores enables balanced characteristics of the treated and the untreated sample if there is sufficient overlap of the propensity scores of both groups. Compared with a conventional direct matching procedure the problem of multidimensionality in finding a corresponding control, for instance related to age, sex, sickness absence duration, pain, depression and others, is thereby reduced to one dimension only.

The propensity score will be estimated by a logistic regression model including all variables that are associated with the treatment allocation. For every WMR participant a patient with a similar propensity score will be selected from the larger pool of CMR patients. Resampling will be realized without replacement. If necessary to achieve balanced data, a caliper of one-quarter of the propensity score during resampling will be used. For sensitivity analysis, additional matching schemes will be tested (with and without replacement, different calipers, varied number of controls). As an indicator of the bias before and after matching owed to differences related to the observed sample characteristics the standardized percentage bias will be calculated. This is the difference of the sample means in cases and controls relative to the square root of the average of the sample variances in both groups [55]. Multiple imputations will be used to fill in missing data before estimation of the propensity score. The propensity scores for each record will be averaged across the completed datasets, and propensity score matching will be performed with these averaged scores [56].

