## Methods

### Study design

The study is a cohort study under real-life conditions with two parallel groups. Participants will either receive a WMR or a CMR program in one of the 256 approved rehabilitation departments. The allocation ratio is determined by the actual allocation under real-life conditions of rehabilitation service provision in Germany. The current ratio of WMR to CMR patients is approximately one to five. The investigators will not have any influence on allocation decisions. Current utilization of WMR is still considerably below the estimated number of patients who need it. Therefore, comparable controls are available who receive a CMR, though their severe restrictions in terms of work ability would also justify participation in a WMR program. Although the researchers have no influence on the allocation procedure they will have the opportunity to model treatment allocation by observed data. Thus propensity score matching will be used to identify controls that are comparable to treated WMR patients and to estimate the unbiased effects of the relative effectiveness of WMR compared with CMR. As randomized controlled trials confirmed the relative efficacy of WMR in trials with high treatment fidelity and carefully selected patients, and implementation of WMR is completed, we assume the superiority of WMR.

Baseline data will be assessed after approval of the rehabilitation program but before the patients begin their rehabilitation. Follow-up data will be assessed three and ten months after their discharge from the rehabilitation center. Moreover, administrative data records will be used. Additionally, department characteristics will be assessed by a departmental survey. No one will be blinded before, during or after the trial.

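### The matching caliper is set at a quarter of the propensity score itself; it names no standard deviation or scale, so it fixes no usable matching distance

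*Protocol article*

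**What the plan says.** In the protocol article, Propensity score matching, the score is defined as a probability: "The propensity score is the conditional probability of receiving the treatment under evaluation (i.e. WMR) given the vector of observed background variables". The basic scheme is nearest-score selection: "For every WMR participant a patient with a similar propensity score will be selected from the larger pool of CMR patients", and "Resampling will be realized without replacement". The caliper is conditional. It opens with "If necessary to achieve balanced data" and continues "a caliper of one-quarter of the propensity score during resampling will be used". No SD of the score and no probability or logit scale is named for it.

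The same section has two safeguards. Before and after matching "the standardized percentage bias will be calculated", and as sensitivity analyses "additional matching schemes will be tested (with and without replacement, different calipers, varied number of controls"). Under Study design, "The current ratio of WMR to CMR patients is approximately one to five", which puts the mean score near 1/6. Under Sample size estimation, 900 WMR and 4,500 CMR patients are expected at ten months, and 900 + 900 are to be analysed after one-to-one matching.

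**The concern.** A caliper is the largest difference in score allowed within a pair. To be usable it needs a scale and a fixed width, normally a fraction of the spread of the score. A quarter of the score is neither. Two programmers could implement the sentence differently, one with 0.25 on the probability scale and the other with 25% of each patient's own score, and obtain different primary samples. The article fixes this rule itself, so this is not detail deferred to an analysis plan.

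At stake is balance in the matched sample. The design is non-randomized, the protocol treats allocation bias as its main threat, and the match is its principal answer. The patients for whom WMR is intended (long sick leave, poor return-to-work expectation, unemployment) would tend to have high scores. Close controls are scarcest there, and the own-score reading is loosest there.

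**Working it through.** **The plan's own figure.** The caliper has no figure to reproduce, but the stated detectable effect depends on how many pairs are kept. Design effect: 1 + (7 − 1) × 0.05 = 1.30. Effective n per group: 900/1.30 = 692.3. Detectable SMD with two-sided alpha 0.016 and power 0.80: (2.409 + 0.842) × √(2/692.3) = 0.1747. The stated 0.175 is reproduced, and it assumes that all 900 WMR patients are matched.

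**Width, absolute reading (0.25).** A variable between 0 and 1 with mean 1/6 has SD at most √(1/6 × 5/6) = 0.373. One-quarter SD is therefore at most 0.373/4 = 0.093, and 0.25/0.0932 ≈ 2.7. This bound needs no assumption about the shape of the score. A WMR patient at the mean score could be paired with any control from 0 to 0.167 + 0.25 = 0.417.

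**Width, own-score reading (0.25 × score).** Let μ be the mean and σ the SD of a calibrated score. The mean among treated patients is μ + σ²/μ. The caliper there, relative to 0.25σ, is (μ + σ²/μ)/σ = μ/σ + σ/μ, which is never below 2. The width also varies by patient: a score of 0.05 gets 0.0125 and a score of 0.60 gets 0.15. It is narrower than one-quarter SD for anyone whose score is below the SD.

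**Residual imbalance.** The documents give no score distribution, so it was assumed: normally distributed logit score, 900 WMR and 4,500 CMR, greedy one-to-one nearest-neighbour matching without replacement, with separation of the groups varied. Entries are the standardized bias of the logit score after matching (pre-matching SD).

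| AUC (assumed) | Score SD | No caliper | 25% of own score | Absolute 0.25 | 0.25 SD of score | WMR matched under 0.25 SD |
|---|---|---|---|---|---|---|
| 0.64 | 0.07 | 0.1% | 0.1% | 0.1% | 0.0% | 99.8% |
| 0.75 | 0.13 | 3.3% | 1.3% | 2.5% | 0.1% | 96.7% |
| 0.82 | 0.18 | 15.9% | 3.5% | 6.4% | 0.3% | 87.5% |
| 0.87 | 0.21 | 31.2% | 4.8% | 8.4% | 0.5% | 77.6% |
| 0.93 | 0.26 | 59.8% | 6.9% | 10.5% | 1.0% | 60.0% |

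Bias before matching ran from 49% to 203%. Over these scenarios the own-score caliper was 2.0 to 2.8 times one-quarter SD at the treated mean, and the absolute caliper 3.9 to 14.6 times.

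**Effect on the detectable SMD.** With the design effect held at 1.30, the figure scales with 1/√(share matched): 0.1747/√0.967 = 0.178 at AUC 0.75 and 0.1747/√0.875 = 0.187 at AUC 0.82.

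**The case against.** The strongest case against is that the wording is defective but does little harm. The caliper is only an upper limit on nearest-score matching from a pool five times larger. The Background expects substantial overlap between the groups and reports that allocation followed the guideline only in part. Under Study design, WMR use is said to fall short of need, so comparable controls exist. In that setting the literal readings leave at most 2.5%. Every outcome model includes the baseline score of its outcome, balance is measured after matching, and other calipers will be tried. All of this stands, and it limits the size of the point.

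Three stronger readings are not supported:

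- A reader might infer that the rule is several times too wide throughout. That fits the absolute reading. The own-score reading is about 2 to 3 times at the treated mean and too narrow for low scores.
- A reader might infer that the matched sample will remain confounded and the primary comparison be biased against WMR. The imbalance depends on an unstated score distribution, and the simulation stops at the score; no bias in an outcome has been shown.
- A reader might take it as established that the authors meant the SD. That is plausible, but the article does not say so.

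Conditional use of the caliper is also a legitimate choice, since it can keep all treated patients. A numeric balance limit can be left to the analysis plan.

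What the objection does not rescue is the sentence itself. Sensitivity analyses vary the primary rule; they do not define it.

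**Conclusion.** The point holds as a misdefined rule in the step that forms the primary matched sample. The two width bounds (at least 2.7 times one-quarter SD if absolute; at least twice at the average WMR patient if relative) rest only on a mean score of about 1/6 and, for the second, on a calibrated score. The imbalance figures rest on an assumed normal logit score and cover measured variables only. On that basis the wording can leave avoidable imbalance of about 3.5 to 10.5% if the groups separate strongly (AUC 0.82 to 0.93), where one-quarter SD would leave 0.3 to 1.0%. At the overlap the protocol anticipates the difference is small. It is worth correcting before matching because the text cannot be implemented unambiguously, not because the result is shown to be biased.

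**What to change.** Restate the caliper as one-quarter of the standard deviation of the propensity score, or of its logit, and say which. Either removes the ambiguity; on the logit scale the simulated residual bias was 0.3% at AUC 0.75 and 0.9% at AUC 0.82. Report how many WMR patients go unmatched. Whether the caliper is always applied, and which balance limit triggers it, can be set in the analysis plan.

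The wording costs a sentence. The real cost is in pairs: where the caliper is applied, about 3.3% of WMR patients go unmatched at AUC 0.75 and 12.5% at AUC 0.82. The own-score reading would already lose 1.5% and 9.5% in the same scenarios (98.5% and 90.5% matched). The 900 + 900 under Sample size estimation should therefore be described as a maximum, and the estimate as applying to the WMR patients who were matched.

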#### Multilevel regression analyses

Analyses of treatment effects in propensity score matched samples can use the same statistical methods as those used in experimental studies [48, 49]. Multilevel regression analyses will be used to account for dependencies in the data [57, 58]. Individual patient data will be conceptualized as level-1 parameters and the rehabilitation department as a level-2 variable. All models will include the treatment variable (WMR vs. CMR), the baseline score of the respective outcome measure and a random intercept which reflects the rehabilitation department. For the primary outcomes, p-value will be fixed at 0.016 (Bonferroni corrected for three outcomes). For the secondary outcomes, p-value will be fixed at 0.05. Linear models will be used for continuous outcomes and logistic models for binary outcomes.

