#### Primary outcomes

The primary outcomes of this study are sick leave duration, stable return to work, and subjective work ability. Evaluation of the effectiveness of WMR relates to the 10-month follow-up. These three outcomes will also be assessed at the three-month follow-up and if appropriate at baseline.

To assess the duration of sick leave, the participants will be asked to report the number of weeks they have been off work for health reasons since discharge from the rehabilitation center. At baseline this question is related to the last 12 months. Stable return to work has been defined in accordance with Kuijer and colleagues [27] as a minimum of four weeks of employment without sick leave. Subjective work ability will be assessed by the Work Ability Score (WAS), which is the first item of the Work Ability Index (WAI) [28]. It compares current subjective work ability with the lifetime best. The 11-point scale ranges from zero (complete incapacity to work) to ten (lifetime’s best work ability). The WAS is highly correlated with the overall WAI score [29].

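### The primary outcome models name one patient-level covariate, so no regression adjustment is stated for imbalance left after matching, and the baseline covariate for stable return to work is not settled

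*Protocol article*

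**What the plan says.** Under Multilevel regression analyses, the protocol article specifies: "All models will include the treatment variable (WMR vs. CMR), the baseline score of the respective outcome measure and a random intercept" for the rehabilitation department. No other covariate is named. Linear models serve continuous outcomes and logistic models serve binary ones.

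Confounding is dealt with under Propensity score matching: "The propensity score will be estimated by a logistic regression model including all variables that are associated with the treatment allocation". Standardized percentage bias is calculated before and after matching. The stated response to imbalance is: "If necessary to achieve balanced data, a caliper of one-quarter of the propensity score during resampling will be used". The sensitivity analyses there vary replacement, caliper and number of controls.

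The section Other measures gives the remaining instruments two uses: "Additional measures will be assessed as potential effect modifiers and as variables for calculating the propensity score". They include the SIMBO, of which the article says: "Higher scores indicate a higher risk of not returning to work and a stronger need for WMR". Moderator analyses use patient characteristics in interaction terms and are labelled exploratory.

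On baseline values of the primary outcomes, the text says: "These three outcomes will also be assessed at the three-month follow-up and if appropriate at baseline". Table 2 marks a baseline measurement for all three, including stable return to work.

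**The concern.** Allocation is not random. By the Background section, the guideline directs patients with long sick leave, poor return-to-work expectation or unemployment to the work-related programme. By the Participants section, a screening for the risk of not returning to work may inform the decision. The drivers of allocation are thus also likely predictors of the primary outcomes, and imbalance that survives matching would bear on the effect estimate.

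The stated plan guards against this at the matching stage only. Three features leave room for imbalance:

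- Score variables are selected by association with allocation, not with outcome.
- No balance threshold is given.
- No sensitivity analysis changes the outcome model, so none tests the result against a misspecified propensity model.

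Stable return to work has a further difficulty. Its model requires a baseline score, but the article does not say what a return to work means before rehabilitation has begun.

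**Working it through.** **1. The plan's own figure.** Inputs from Sample size estimation: 900 per group, cluster size 7.0, intracluster correlation 0.05, power 0.80, alpha 0.016.

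- Design effect = 1 + (7 − 1) × 0.05 = 1.30.
- Effective n per group = 900 / 1.30 = 692.3.
- Standard error of the SMD = √(2 / 692.3) = 0.0537.
- Detectable SMD = (z for two-sided 0.016 + z for power 0.80) × 0.0537 = 0.1747.

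The stated 0.175 reproduces. It takes no credit for covariates, so nothing below undermines the planned power.

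**2. Precision (linear outcomes only).** The article gives no covariate strength, so R² is assumed. It is the share of the outcome variance behind the 0.175 that the extra covariates explain, with the intracluster correlation unchanged. Detectable SMD = 0.175 × √(1 − R²); equivalent gain in patients = 1 / (1 − R²) − 1.

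| Added R² (assumed) | Detectable SMD | Equivalent gain in patients | Power at 0.175 |
|---|---|---|---|
| 0 | 0.175 | – | 0.80 |
| 0.10 | 0.166 | 11% | 0.85 |
| 0.20 | 0.157 | 25% | 0.89 |

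This formula does not carry over to the logistic model. Adding prognostic covariates there generally raises the standard error of the log odds ratio.

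**3. Bias.** Bias = residual imbalance (SD) × standardized outcome slope given the baseline outcome. Both inputs are assumed: imbalance 0.05 to 0.10, slope 0.1 to 0.5.

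- Smallest: 0.05 × 0.1 = 0.005 SD; 0.005 / 0.175 = 3% of the detectable effect.
- Largest: 0.10 × 0.5 = 0.05 SD; 0.05 / 0.175 = 29%.
- With a standard error of 0.0537 and no true effect, the actual two-sided type I error at nominal 0.016 would be 0.0165 to 0.070.

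This is for one covariate; several may add or cancel. It applies to a systematic difference, since a chance difference is already covered by the standard error.

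**4. Stable return to work.** Side by side:

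- Multilevel regression analyses requires a baseline score in every model.
- Table 2 marks a baseline measurement for this outcome.
- Primary outcomes makes baseline assessment conditional for all three outcomes.
- Study design places baseline before rehabilitation starts.
- The definition is at least four weeks in work with no sick leave, with no separate pre-rehabilitation wording.

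The four-week criterion could be applied before rehabilitation. It would then give the same value to an unemployed patient and to an employed patient on sick leave, which makes it a coarse covariate for this outcome.

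**The case against.** The strongest reply is that imbalance is handled by design. The prognostic instruments are collected for the propensity score and moderator analyses, balance is measured, a caliper is available, and other matching schemes are tried. Matching followed by a model with few terms is a recognised approach, and the article states that rationale with citations. The model sentence lists what will be included and does not exclude more; a condensed article may leave further covariates to an analysis plan that is not shown.

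Much of this stands. A reader might infer three stronger things that the documents do not support:

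- **That the prognostic factors go unused.** Other measures, Propensity score matching and Moderator analyses each give them a role.
- **That residual imbalance is left with no remedy.** The conditional caliper and the alternative matching schemes are remedies; what is not stated is a regression one.
- **That stable return to work has no usable baseline.** Table 2 plans one, and the conditional wording covers all three primary outcomes without singling this one out.

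It is also fair that the sizes above rest on assumed inputs.

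The reply does not remove the core. The article fixes a model form for all outcomes and names one patient-level covariate. Its selection rule for the score can pass over a prognostic variable with a weak link to allocation. None of the listed remedies acts in the outcome model.

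**Conclusion.** The point holds as a low-cost improvement to robustness and precision, not as an error in the plan. The stated detectable SMD and the planned power are sound.

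For sick leave duration and work ability, further adjustment would bring the detectable SMD to about 0.166 to 0.157 if the added R² is 0.10 to 0.20. The protection against bias is worth 0.005 to 0.05 SD under the assumed imbalance and slope. Neither range can be narrowed from the document. For stable return to work, the case rests on protection against imbalance and on a properly defined baseline covariate, not on a narrower interval for the log odds ratio. The statements on its baseline need to be reconciled in any case.

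**What to change.** 1. Prespecify one fixed covariate set for the three primary outcome models: baseline sick leave weeks, employment status, current sick leave, Work Ability Score, SIMBO score, subjective prognosis of employment, age and sex. All are already collected at baseline.
2. For stable return to work, use baseline employment and sick-leave status as the baseline covariates. Bring Table 2, Primary outcomes and Multilevel regression analyses into line with this.
3. For that outcome, report a covariate-standardized risk difference beside the odds ratio.
4. Keep adjustment for any further covariate chosen by a post-matching imbalance threshold as a sensitivity analysis only. Such a rule makes the covariate set depend on the data and should not define the primary model.

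The cost is wording in the analysis plan, with no new data. Fixing the set in advance also rules out later covariate selection in a study where no one is blinded. The one downside is that the odds ratio becomes conditional on the covariates, which the standardized risk difference addresses.

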### Sample size estimation

We expect to find small mean differences between WMR and CMR in primary outcomes. For three months, of about 18,000 insured patients with permission for a musculoskeletal rehabilitation program 15,000 will receive CMR and 3,000 will receive WMR. We expect a participation rate of 40 %, i.e. 7,200 patients (6,000 CMR, 1,200 WMR) at baseline. At the 10-month follow-up, we expect a dropout rate of 25 %, i.e. 900 patients with WMR and 4,500 CMR left. Using a one-to-one match without replacement, 1,800 patients (900 WMR, 900 CMR) will be analyzed. Assuming a number of clusters (departments) *k* = 256 (with 176 departments providing CMR and 80 departments providing additionally WMR), a cluster size of *m* = 7.0, an intracluster correlation of rho = 0.05, a power of 0.80 and a Bonferroni corrected *p*-value = 0.016, an effect of SMD = 0.175 can be detected (Fig. 1).

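### WMR runs in only 80 of 256 departments, so the random-intercept model lets part of any difference between WMR-offering and CMR-only departments into the WMR estimate

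*Protocol article*

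**What the plan says.** *Sample size estimation* puts the departments at 256, "with 176 departments providing CMR and 80 departments providing additionally WMR". From a baseline sample of 1,200 WMR and 6,000 CMR patients, "we expect a dropout rate of 25 %, i.e. 900 patients with WMR and 4,500 CMR left". The matched set follows: "Using a one-to-one match without replacement, 1,800 patients (900 WMR, 900 CMR) will be analyzed".

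*Propensity score matching* picks each control from the whole CMR pool, with no restriction by department or department type. The propensity model is described generally, as containing every variable related to allocation. The examples given there, and the items that *Other measures* assigns to the score, are patient-level.

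*Multilevel regression analyses* fixes what all models contain: treatment, the baseline score of the outcome, and "a random intercept which reflects the rehabilitation department".

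*Department characteristics* plans further data collection: "A survey of the departments will assess additional data on the department level (e.g. staff, team cooperation, and infrastructure". The only analytic use stated for such data is in *Moderator analyses*, as exploratory modifiers of the treatment effect.

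*Study design* and *Propensity score matching* both describe the resulting estimates as unbiased.

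**The concern.** A random intercept handles the correlation of patients within a department. It does not remove confounding by department, because it treats department effects as independent of the covariates, including treatment. Here that independence is doubtful by construction: every WMR patient sits in one of 80 departments, while many controls will sit in the other 176.

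Suppose WMR-offering departments have better or worse outcomes for reasons unrelated to the WMR programme, such as setting or size. The model then corrects for this only in part, and patient-level matching does not correct for it at all. *Multilevel regression analyses* justifies the model by saying that matched samples can be analysed like experimental ones. That covers the patient characteristics that were balanced, not the department. An advantage of WMR-offering departments would look like a WMR effect, and a disadvantage would hide one. The planned sensitivity analyses vary replacement, calipers and number of controls, and none of these addresses department type.

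**Working it through.** **1. The plan's own figure.** Inputs from *Sample size estimation*: 900 per arm, "a cluster size of *m* = 7.0", "an intracluster correlation of rho = 0.05", "a power of 0.80 and a Bonferroni corrected *p*-value = 0.016".
- Design effect: 1 + (7.0 − 1) × 0.05 = 1.30. Effective n per arm: 900/1.30 = 692.
- Detectable SMD: (2.409 + 0.842) × √(2/692) = 0.175. The stated value is reproduced with two-sided alpha 0.016.
- 1,800/256 = 7.03, which matches m = 7.0. The matched set is therefore planned to span all 256 departments, including those without WMR.

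**2. The missing input.** The share *s* of matched controls treated in the 80 WMR-offering departments is not given. Two simple assumptions:
- Equal CMR volume per department: s = 80/256 = 31.25%, which is 4,500 × 80/256 ≈ 1,406 CMR patients in the pool.
- Equal total volume per department: 5,400 × 80/256 − 900 ≈ 787 CMR patients, so s = 787/4,500 = 17.5%.

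**3. Share of a department-type difference that enters the WMR coefficient.** Generalised least squares for a linear random-intercept model with treatment. The baseline score is left out, since matching should balance it. Each WMR-offering department has w = 900/80 = 11.25 WMR patients and c = 900s/80 controls, so n₁ = w + c. Each CMR-only department has n₀ = 900(1 − s)/176 controls. With fⱼ = ρ/(1 − ρ + nⱼρ):
- a = 80w(1 − f₁n₁)
- b = 80(w − f₁w²)
- A₁ = 80n₁(1 − f₁n₁)
- A₀ = 176n₀(1 − f₀n₀)
- D = (A₁ + A₀)b − a²
- share = aA₀/D
- SE = √[(1 − ρ)(A₁ + A₀)/D]

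For s = 31.25% and ρ = 0.05: n₁ = 14.77, n₀ = 3.52, f₁ = 0.0296, f₀ = 0.0444, a = 506.4, b = 600.1, A₁ = 664.7, A₀ = 522.1. Share = 506.4 × 522.1/(1,186.8 × 600.1 − 506.4²) = **0.58**, and SE = 0.0497.

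| Share of controls in WMR-offering departments | Share of the difference entering the estimate (ρ = 0.05) |
|---|---|
| 10% | 84% |
| 17.5% | 73% |
| 31.25% | 58% |
| 40% | 50% |
| 50% | 41% |
| 75% | 22% |

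At s = 31.25% the share is 66% for ρ = 0.01, 49% for 0.10 and 37% for 0.20.

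**4. Illustration with an assumed department difference.** The plan's ρ implies a department SD of √0.05 = 0.22. Take s = 31.25%, no true effect and nominal alpha 0.016:
- Difference 0.10 SD: bias 0.058, one third of 0.175. False-positive rate about 11%.
- Difference 0.15 SD: bias 0.087. About 26%.
- Difference 0.20 SD: bias 0.116, or 66% of 0.175. About 47%.

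**5. With a fixed indicator for WMR-offering departments.** The share becomes zero, because the contrast then rests on WMR and CMR patients inside the 80 departments. Detectable SMD = 3.25 × √[0.95/(80wc/(w + c))]:
- s = 31.25%: 3.25 × √(0.95/214.3) = 0.216
- s = 17.5%: 3.25 × √(0.95/134.0) = 0.274
- s = 50%: 0.183

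**The case against.** **The number is conditional.** A reader might infer that more than half of any department difference is always counted as treatment effect. The documents do not support that. They do not give the split of controls, and the share falls below one half once about 40% of controls come from WMR-offering departments, or at ρ = 0.10 with an even CMR spread. This objection stands in full.

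**No department difference is documented.** Nothing in the protocol shows that WMR-offering departments do better or worse for other reasons. The false-positive rates in step 4 rest on assumed differences, and the sign could go either way. This also stands.

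**The wording may leave room for department variables.** The propensity model is to include all variables related to allocation, and a list of required model terms does not forbid others. Structural features could enter under that wording. WMR-offering status itself could not usefully enter the propensity score: patients in CMR-only departments would have a propensity of zero and drop out, against k = 256 and m = 7.0. As written, no department-level adjustment is planned, while the estimates are called unbiased. The objection softens the point but does not remove it.

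**Stronger remedies carry their own risks.** CMR patients in WMR-offering departments may have received some WMR content, or may have been judged not to need WMR. Preferring them as controls could dilute the effect or worsen confounding by indication. Under equal total volume only about 787 such patients exist, fewer than 900. Adjusting for features that are part of WMR delivery could remove some of the effect under study. These points stand and limit the fix.

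**Conclusion.** The point holds as a risk of bias. WMR is confined to 80 departments, controls are planned from all 256, and the specified model assumes away any link between department and treatment. For the linear outcomes at ρ = 0.05, about 58% (even CMR volume) to 73% (even total volume) of a department-type difference would enter the WMR estimate, with 22% to 84% over the wider range of splits. These figures assume equal-sized departments within each type. Stable return to work is analysed with a logistic model of the same structure, for which the share was not computed.

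One might go further and conclude that the trial will report a spurious WMR benefit. The documents do not support this, because the size and direction of any department difference are unknown. Nor is the stated SMD of 0.175 wrong: it reproduces from its inputs. What is not supported is the claim of unbiased estimates where department-level differences are concerned.

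**What to change.** 1. In *Multilevel regression analyses*, add structural department features fixed before treatment as level-2 covariates in the primary outcome models: inpatient or outpatient, owned by the Federal GPI or mainly occupied by it, and size. Leave out features that may be part of WMR delivery, such as staffing for work-related modules. This reduces the risk only as far as these features explain the department difference.
2. Prespecify a sensitivity analysis that adds a WMR-offering indicator, or uses a within-department treatment contrast, and report it beside the primary model.
3. Report the share of matched controls treated in WMR-offering departments, so that readers can place the result in the table above.
4. In *Study design* and *Propensity score matching*, limit the claim of unbiasedness to measured patient-level confounding.
5. If matching preferentially to controls in WMR-offering departments is of interest, make it at most one more scheme among the matching sensitivity analyses.

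The cost is mainly plan wording. Setting and institution type are already described, and the number of treated patients is among the planned department measures. Recruitment was still ongoing at publication. The price of the indicator analysis is precision: a detectable SMD of about 0.216 to 0.274 against 0.175. Because its controls may also have received some WMR content, it should accompany the primary model and not replace it.
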